### (2) Classification of Research

■Research conducted independently by Saitama Medical Center, Jichi Medical University

### 3. Purpose and Significance of the Research

#### (1) Purpose

- To clarify the prevalence of SARS-COV-2 antibodies among healthcare workers at our center.
- To clarify the characteristics of SARS-COV-2 antibody-positive patients.

#### (2) Significance

- IgG antibody-positive patients are predicted to have a low risk of reinfection, at least in the short term. This information is particularly useful for health care workers during the COVID-19 pandemic in terms of nosocomial infection prevention.

### 4. Research Methods and Duration

#### Research Methods

##### Research Design

- Clinical Research
- Observational research

#### Specific Outline

- The subject shall be from volunteers recruited by posting posters in the Research Implementation Section and Research Cooperation Section. An email shall be sent to staff members who have expressed interest in volunteering, and if they respond to the email, they shall be considered to be willing to participate.
- The researcher shall explain the research directly to the volunteers who responded to the email and give them the explanation and consent forms.
- At a later date, the volunteer who signed the consent form shall be the research subject (doctor or nurse).
- Blood samples shall be collected from all the subjects at the start of the research, one month after the start of the research, and two months after the start of the research, and the serum shall be frozen and stored. Two to four weeks after the start of the research, each of the stored specimens at the start of the research shall be subjected to a qualitative test for SARS-CoV-2 IgG/IgM antibodies by immunochromatography. Three months after the start of the research, the same qualitative test shall be performed on each of the remaining specimens.
- A research reagent, (the Novel Coronavirus Antibody Test Kit (COVID-19 IgG/IgM Immunochromatographic Kit, Innovita (Tangshan) Biological Technology Co.) shall be used for antibody testing. For judgment, it shall be confirmed that the control is positive, check the IgG band, and classify the result as "IgG antibody positive," "IgG antibody positive," or "unable to judge. The test results should also be stored in a photograph.

- This research is to determine the history of infection. Therefore, IgM shall not be measured; if a kit with IgM results is used, it shall be labeled so that the results are not visible.
- The results should be visually checked by the Principal Investigator and one of the Research Coordinators, and any matches should be recorded. If the results are inconsistent, a third Research Coordinator shall make the determination.
- This test kit is a research reagent only and it is clearly labeled as "may not be used for therapeutic or diagnostic purposes".
- The percentage of antibody-positive subjects among all the subjects shall be measured.
- Following items as at the time of the research shall be recorded: The subject's age, gender, history of living abroad, city or town of residence, underlying medical conditions, medication history, whether or not they have received medical checkups, smoking history, alcohol consumption history, place of residence within the past year, department of work, BCG intake history, the presence and timing of COVID19 (novel coronavirus infection) in patients under their care (location, date and time), symptoms of the common cold (cough, nasal discharge, sore throat, malaise, taste disorder, respiratory distress) within the last 3 months and the date (how many days before the examination), and the presence of fever.
- Analyze whether there are statistically significant differences in the proportions of these factors among the subjects who test positive for antibodies compared to the subjects who test negative.
- All the subjects shall be asked every month about the presence or absence of airway symptoms, fever, taste disturbance, and COVID-19 diagnosis at a medical institution in the last month. This shall be continued for the duration of the research.
- As of April 6, 2020, there is no antibody test that can guarantee high accuracy. Research on antibody accuracy verification is ongoing worldwide, and it is possible that antibody test kits with verified/guaranteed accuracy will be identified in the future. If antibody tests with proven accuracy are available during the research period, the research reagents may be changed.

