#### Method of Statistical Analysis, Evaluation Items and Methods

##### a. Method of Statistical Analysis

- The actual number of subjects who tested positive for antibodies at the beginning of the research, after 1 month, and after 2 months, and the percentage of all subjects is measured, and 95% confidence intervals is obtained.
- Obtain the aforementioned predetermined factors: The subject's age, gender, history of living abroad, city of residence, underlying illness, medication history, whether or not he or she has received medical checkups, smoking history, drinking history, place of residence within the past year, department of work, BCG intake history, the presence or absence of COVID-19 (novel coronavirus infection) in the patient in charge, history of travel in the last year, the presence or absence of access to cluster infection sites, the presence or absence of the common cold symptoms (cough, nasal discharge, sore throat, malaise, dysgeusia, respiratory distress) within 3 months, and the presence or absence of fever.

The differences in these factors between IgG antibody-positive and antibody-negative subjects are tested by chi-square test, Fisher's exact test, and logistic analysis, and for continuous variables by Mann-Whitney U test and logistic analysis. In addition, the characteristics of the above factors in the research subjects who test positive for antibodies will be described.

- Measure the percentage of antibody-positive individuals who develop COVID-19 after a positive test.

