#### b. Evaluation Items

- The primary outcome is the rate of antibody positivity in the entire research population, and the change in the rate of positivity
- The secondary outcome is the detection of significant differences in each factor among antibody-positive and antibody-negative subjects (age, sex, place of residence, department, the presence of COVID19 in the patient in charge if not an early resident, travel history in the past year, access to cluster-infected areas, the presence of cold symptoms and fever within 3 months), and subsequent incidence of COVID-19 in antibody-positive individuals.

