### 6. Scientific Rationality

- Currently, PCR tests for SARS-CoV-2 infection are less common in Japan than in other countries, and the actual spread of the infection is not known. By detecting antibody positivity, the percentage of previously infected individuals in the control group can be measured.

- Since it is currently difficult to assume the SARS-CoV-2 infection rate, the followings are the subject of the research: Physicians in general medicine and emergency departments who have frequent contact with patients diagnosed with COVID-19 or with patients who complain of respiratory tract symptoms such as the common cold, physicians in ICU, ward and emergency nurses who have actually been involved in the treatment of COVID-19, and junior resident as healthy adults who rotate through multiple departments.
- For statistical analysis, all antibody-positive subjects are assumed to have a history of infection, and the percentage of subjects tested is determined.

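### Two secondary-outcome factors are absent from the list of items to record, and no exposure item is asked again at the 1- and 2-month draws

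*Protocol*

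**What the plan says.** Three places in section 4 of the protocol list the subject factors.

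- **Specific Outline.** The recording list begins "Following items as at the time of the research shall be recorded". It includes department of work and "the presence and timing of COVID19 (novel coronavirus infection) in patients under their care (location, date and time", but neither travel nor cluster sites. No visit is named for its completion.
- **a. Method of Statistical Analysis.** The list begins "Obtain the aforementioned predetermined factors" and includes "history of travel in the last year, the presence or absence of access to cluster infection sites".
- **b. Evaluation Items.** The secondary outcome compares antibody-positive with antibody-negative subjects on a shorter list, which includes "travel history in the past year, access to cluster-infected areas".

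The only repeated data collection other than blood is also in the Specific Outline: "All the subjects shall be asked every month about the presence or absence of airway symptoms, fever, taste disturbance, and COVID-19 diagnosis", with reference to the preceding month.

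Blood is drawn "at the start of the research, one month after the start of the research, and two months after the start of the research", and the change in the positivity rate is part of the primary outcome. The Selection Policy (section 5) admits staff whose work with infected patients is past or still to come. Section 6 describes the "junior resident as healthy adults who rotate through multiple departments" as one of the groups studied.

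**The concern.** There are two linked gaps.

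First, the analysis section points back to factors supposedly listed already, but two of them do not appear in the recording list. A questionnaire built from the Specific Outline would leave out two secondary-outcome factors. Asking about them late would bring some loss of recall.

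Second, the outcome is measured three times, while the factors most likely to change between draws (care of COVID-19 patients, department, travel, cluster access) have no stated repeat. The protocol expects a low positivity rate in April 2020, so later positives may make up much of the comparison. If the questionnaire is completed early, a staff member who first cares for infected patients afterwards and is positive at month 2 would enter the comparison as unexposed. Describing the characteristics of antibody-positive staff is one of the study's two stated purposes, so this affects a core result.

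**Working it through.** The protocol gives no figure on this point to reproduce. The check is an item-by-item comparison of its lists, followed by the direction of any bias.

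**Step 1. Compare the factor lists.**

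| Place in section 4 | Factors | Past-year travel | Cluster-site access |
|---|---|---|---|
| Specific Outline (to be recorded) | 15 | absent | absent |
| Method of Statistical Analysis | 17 | present | present |
| Evaluation Items (secondary outcome) | 9 | present | present |

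The analysis list less the recording list leaves exactly these two factors (17 − 15 = 2). The secondary-outcome list less the recording list leaves the same two, so 2 of 9 secondary factors are not in the recording list. Its nearest entries are having lived abroad and the past year's place of residence; neither covers travel or a visit to a cluster site.

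**Step 2. Look for repeated exposure data.** The monthly questions cover four topics: respiratory symptoms, fever, altered taste and a diagnosis of COVID-19. Exposure items among them: 0 of 4. No other section provides for updating patient care, department, travel or cluster access.

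**Step 3. When is the factor questionnaire completed?** The recording list names no visit, whereas the blood-draw schedule names each time point. Three features favour a single early record:

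- section 7(1) mentions the questionnaire together with the consent form;
- symptoms are dated by days before one examination;
- monthly repetition is stated only for symptoms and diagnosis.

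This is an inference; the protocol does not fix the timing.

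**Step 4. Direction of the bias if the record is early and not updated.** Let E be staff exposed before the questionnaire, L those first exposed after it, and U those not exposed by the draw, with numbers n and risks of a positive result r. The recorded unexposed group combines L and U, so its apparent risk is

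(n_L·r_L + n_U·r_U) / (n_L + n_U) = r_U + [n_L / (n_L + n_U)] × (r_L − r_U).

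If late exposure raises risk (r_L > r_U), this exceeds r_U. The contrast with r_E then shrinks by the late-exposed share of the recorded unexposed group times the excess risk r_L − r_U. The protocol gives neither quantity, so the direction can be argued but the size cannot be computed.

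**The case against.** The strongest reply is that the protocol does not say these data will be missing. The analysis section instructs that both factors be obtained, so the pointer back to an earlier list may simply be a wrong cross-reference. The questionnaire is not shown and may contain both items. This stands: a reader might infer that the two factors will not be collected and cannot be analysed, but the documents show only that the lists disagree. Nor do they show that an omission would be beyond repair, because subjects are staff with contact details on file who are questioned every month.

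Likewise, a reader might infer that exposure is recorded only at the start and that later positives cannot be related to preceding exposure. The protocol says neither. The timing is open, and patient contact is to be recorded with dates, so a form completed or updated after the last draw could place some exposures in time. Against this, dates on an early form cannot cover later contact, and the analysis section reduces the item to presence or absence.

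It is also fair to say that no analysis of seroconversion by prior exposure is stated. The protocol compares positives with negatives without naming the draw. This limits the claim, but it also leaves the outcome's timing as open as the exposure's.

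Finally, with 60 planned subjects and a low expected rate, the comparison will be imprecise however exposure is recorded. That limits the statistical gain. It does not remove the reason to record exposure correctly, since the positives' characteristics are also to be described.

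**Conclusion.** The list mismatch is a plain inconsistency: 2 of the 9 secondary-outcome factors are absent from the recording list, which therefore does not secure their collection.

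The exposure gap also holds. No visit is fixed for the factor questionnaire and none of the four monthly topics concerns exposure, so exposure preceding a 1- or 2-month positive result is not secured. Bias toward no difference rests on three assumptions: the questionnaire is completed early and not updated, some staff are first exposed after it, and late exposure raises the risk of a positive result by the draw in question. Its size is unknown. Any numerical ratio would need an assumed split of exposed, late-exposed and unexposed staff that the documents do not supply, and the eligibility wording leaves unclear how many would remain unexposed.

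The point merits correction before data collection; it does not show that the study's comparisons are invalid.

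**What to change.** 1. Add past-year travel and access to cluster sites to the recording list in the Specific Outline and to the questionnaire, so that the list agrees with the analysis section and the secondary outcome.
2. State that the factor questionnaire is completed at the first blood draw.
3. Add to the existing monthly questions: care of COVID-19 patients since the last contact (with dates), current department, travel and cluster-site access.
4. State that positives and negatives are compared at each draw, using exposure reported up to that draw.

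The cost is a few more questions per subject per month, within a contact already planned. No extra visit or blood sample is needed.

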#### 9. Comprehensive Assessment of Burdens and Anticipated Risks and Benefits to Research Subjects, Measures to Minimize Such Burdens and Risks

(1) Burden Incurred by Research Subjects

1) Cost burden

There is no cost burden on research subjects when they participate in the research.

2) Other burdens

There is no other burden on research subjects when they participate in the research.

(2) Anticipated Risks to Research Subjects

1) Disadvantage ■ None

2) Risks ■ None

3) Discomfort ■ Yes Description: Pain associated with blood collection

(3) Benefits Accruing to the Research Subjects

1) Gratuities to subjects

■ None

2) Other benefits

■ No

(4) A comprehensive Assessment of the Burdens and Anticipated Risks and Benefits to Research Subjects, and Measures to Minimize Such Burdens and Risks

1) Overall evaluation

- The possibility of direct disadvantage or benefit to the research subjects is low.

2) Measures to minimize burden and risk

Minimize pain during blood collection.

- The pain during the blood collection process should be minimized
- The test should be performed during or after work breaks to minimize the possibility that work may be interfered
- There is a possibility of interference with work due to infectivity evaluation (PCR test, etc.) in the case of antibody positivity. Therefore, by allowing a period of one month from the time of blood collection to the time of antibody measurement, the infectivity evaluation shall be unnecessary and the burden shall be eliminated.
- In order to minimize the psychological burden of knowing the results, the results shall be disclosed only to those who wish to receive them.

3) Compensation for loss

There shall be no compensation for losses incurred through the implementation of this research.

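### The subject's own earlier COVID-19 is not asked for and later diagnoses are undated, so the infection that produced the antibody can be counted as subsequent COVID-19

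*Protocol*

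**What the plan says.** **Outcome.** Under Method of Statistical Analysis the protocol plans to "Measure the percentage of antibody-positive individuals who develop COVID-19 after a positive test". Evaluation Items names the "subsequent incidence of COVID-19 in antibody-positive individuals" as part of the secondary outcome. Both depend on the order of two events. No starting point (draw or assay) is stated, and no rule separates the infection that produced the IgG from a new one.

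**Start-of-study data.** The COVID-19 item in the Specific Outline concerns patients, not the subject: "the presence and timing of COVID19 (novel coronavirus infection) in patients under their care (location, date and time". Cold symptoms are dated: "within the last 3 months and the date (how many days before the examination". Neither this list nor the repeated list under Method of Statistical Analysis names the subject's own COVID-19 diagnosis or PCR result.

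**Follow-up data.** The only stated source of later cases is the monthly question, which covers a "COVID-19 diagnosis at a medical institution in the last month" and is answered as present or absent.

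**Entry.** Selection Policy excludes people with fever, cough or respiratory distress at the first examination. It does not exclude people who have recovered, or who are infected without those three symptoms.

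**Timing.** Blood is drawn at the start and at one and two months. Start sera are assayed at two to four weeks and the remaining sera at three months.

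**The concern.** A percentage of positives who later develop COVID-19 can be read only if each diagnosis can be placed before or after the positive sample, and if a diagnosis of the same episode can be told from a new one. The data as specified allow neither reliably. Scientific Rationality treats every positive as already infected, so a diagnosis that merely confirms that infection would look like an infection despite antibody. The Significance section predicts low reinfection risk in IgG-positive people, and this rate is the only planned result that bears on it.

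The gap lies in data capture. An analysis plan can define what counts as subsequent, but it cannot supply dates or history that were never collected.

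**Working it through.** **1. The plan's own figure.** The sample size follows from n = z² p(1 − p) / e², with z = 1.96 and e = 0.10.
- p = 0.10: 3.8416 × 0.09 / 0.01 = 34.57, rounded up to 35.
- p = 0.15: 3.8416 × 0.1275 / 0.01 = 48.98, rounded up to 49.

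Both stated figures reproduce when 10% and 15% are read as positive rates with a 10-point margin. Reading 15% as the margin gives 16 or 22, which does not match. Rounding 49 to 50 and adding 10 withdrawals gives 60. The point does not rest on this calculation; it supplies the range of 50-60 subjects used in step 4.

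**2. Draw and assay times (Specific Outline).**

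| Sample | Assayed | Gap from draw to assay |
|---|---|---|
| Start | 2-4 weeks | 2-4 weeks |
| 1 month | 3 months | 3 − 1 = 2 months |
| 2 months | 3 months | 3 − 2 = 1 month |

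**3. Where the order can fail.**
- *Positive at the start, question asked at one month.* The look-back covers days 0-30, all after the draw, so 0/30 = 0% of it precedes the sample. The remaining error is an infection in progress at the draw and diagnosed later. As written, it counts as subsequent COVID-19.
- *Positive at the start, first question asked at or soon after the start.* The look-back then reaches before the draw. A subject already diagnosed would answer that a diagnosis is present, and no item on the subject's own history would reveal the order.
- *Positive at one or two months.* If the question is asked on the day of the draw, a reported diagnosis is known to precede it. The protocol does not tie the question to the draw. Asked at another time, the one-month window can span the draw, and a diagnosis made before it can be taken as following it. The entry symptom exclusion does not apply to these draws.
- *Diagnosis between one of these draws and the month-3 assay.* It is subsequent if counted from the draw and not if counted from the assay.

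**4. Effect of one misplaced case.** The documents give no expected number of positives, so positive rates of 5%, 10% and 15% are assumed. The 10% and 15% come from step 1, and 5% is the level below which the protocol may recruit more subjects. With k positives, one wrongly counted case changes the rate from 0/k to 1/k. Limits are exact (Clopper-Pearson) 95%.

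| Subjects | Rate | k | Upper limit for 0/k | 1/k | 95% limits for 1/k |
|---|---|---|---|---|---|
| 50 | 5% | 2 (from 2.5) | 84.2% | 50.0% | 1.3-98.7% |
| 50 | 10% | 5 | 52.2% | 20.0% | 0.5-71.6% |
| 50 | 15% | 8 (from 7.5) | 36.9% | 12.5% | 0.3-52.7% |
| 60 | 5% | 3 | 70.8% | 33.3% | 0.8-90.6% |
| 60 | 10% | 6 | 45.9% | 16.7% | 0.4-64.1% |
| 60 | 15% | 9 | 33.6% | 11.1% | 0.3-48.2% |

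The shift is 11 to 50 percentage points. If 2.5 positives is taken as 3 instead of 2, the top of the range is 33%.

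**The case against.** **The information may be collected anyway.** Section 7 mentions a separate questionnaire that is not shown, and the item on underlying conditions could draw out an earlier diagnosis. The correspondence table in section 8 would let the team go back to the few staff concerned. This is fair, but the protocol requires none of it for this outcome.

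**The counting rule belongs in an analysis plan.** That is partly right, and such a plan may exist. It does not apply to the missing dates and history.

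**The scenario is narrow and the outcome is imprecise anyway.** At the start it needs someone IgG positive, still infected, free of the three excluded symptoms, and then diagnosed where PCR is uncommon. The documents give no basis for a probability. A correct 0/3 already has an upper limit of 71%. Both remarks stand. However, the interval shows the imprecision, whereas nothing in the results would show a misplaced case.

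**Stronger readings that a reader might infer.**
- *Most of the first month's look-back precedes the test.* Counted from the kit reading, the share would be 14/30 = 47% to 28/30 = 93%. But frozen serum describes the day of the draw, and none of days 0-30 precedes the start draw.
- *The protocol expects positives to be sent for PCR.* Section 9 says "There is a possibility of interference with work due to infectivity evaluation (PCR test, etc.) in the case of antibody positivity", but its next sentence says that the delay before measurement is meant to make this evaluation unnecessary. That delay was chosen to spare staff disruption, so it is also no basis for a one-month limit separating reinfection from the same episode.
- *The study promises to separate diagnosed from unrecognised infection.* Scientific Rationality says only "By detecting antibody positivity, the percentage of previously infected individuals in the control group can be measured". The split would be useful, but it is not a stated aim.

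**Conclusion.** The point holds as a defect in data capture for one part of the secondary outcome. As written, a late diagnosis of the infection that produced the IgG counts as subsequent COVID-19. For the 1- and 2-month samples, diagnoses can be misordered if the monthly question is not asked at the draw. The antibody positivity rate, its change over time and the sample size are unaffected. The two listed purposes, prevalence and characteristics of positives, do not depend on this rate.

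One such case would raise the rate from 0% to between 11% and 50%. This rests on an assumed 5-15% positivity in 50-60 subjects and on no other cases among the positives. It is the consequence if a case occurs, not an estimate of how often one would. Additional recruitment that raised the number of positives would reduce it.

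**What to change.** - **Specific Outline, start-of-study items:** add the subject's own earlier COVID-19 diagnosis or PCR test, with date and result.
- **Specific Outline, monthly question:** add the dates of symptom onset and of diagnosis.
- **Method of Statistical Analysis:** count subsequent COVID-19 from the date of the positive blood draw. List diagnoses with onset on or before that draw separately as same-episode. Show the draw-to-onset interval for each remaining case, so that readers can judge it without a fixed cut-off. Describe start-of-study positives by whether they had been diagnosed before.

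The cost is a slightly longer questionnaire and a short definition. No extra blood draw and no change in sample size is needed. An infection without symptoms has no onset date, so its diagnosis date would have to be shown instead, and some such cases will stay ambiguous.
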